### Power calculations and sample size

By setting target sample sizes of 170 subjects per arm, the effectiveness sub-study was designed to provide 80% power to detect between-arm (pairwise) differences in the proportion receiving CIDC of 15 percentage points and standardized differences of 0.3 standard deviations (sd) in the mean levels of continuous outcomes, under two-sided testing with alpha = 5% [71]. For the sub-study focusing on non-depressed patients, the target enrollment of 102 subjects per arm provides 80% power to reject the noninferiority null hypothesis that exposure to an experimental intervention groups (N = 204 in the PSA/IMCP groups) is associated with at least a 3.5 percentage point increase in the extremely low risk anticipated for antidepressant prescribing in the control group (N = 102), under one-sided testing with alpha = 5% and assuming that the true risk is 1% in each of the three groups [72]. For pairwise comparisons of means, a sample size of 102 in each arm of the non-depressed sub-study provides greater than 80% power to detect differences of 0.4 sd [71].

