### Sub-study 1: patients *with* clinically significant depressive symptoms

This sub-study involves a sample of approximately 500 patients with a Patient Health Questionnaire-9 (PHQ-9) score of ≥ 5 (mild or greater depressive symptoms) on the previsit survey.

**Key Outcome: Initial Depression Care** The key process of care measure is a composite outcome termed *Components of Initial Depression Care (CIDC).* CIDC is coded positive if an antidepressant prescription or mental health referral is provided at the index study visit among the subset of participants with a high likelihood of clinically significant depression (defined as a baseline PHQ-9 score ≥ 10). This outcome is defined as “key” based on the primary study goal, which is to increase patient engagement in care at the initial visit. For patients with clinically significant depression, evidence supports the use of antidepressants and/or psychotherapy or counseling [58-60], and the study was powered to detect a significant intervention effect on this outcome. It is hypothesized that the active interventions will result in a greater likelihood that physicians will offer and patients will accept these treatments.

**Other outcomes** Other outcomes pertinent to Sub-study 1 include effects of the two active interventions on primary care follow-up interval; self-reported physical and mental health at 12 weeks; patient engagement with care during and immediately after the index visit and patient self-efficacy for communication immediately after the index visit; depression-related stigma immediately after the index visit and at 12 weeks; and suicide inquiry by the physician during the index visit.

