**Sub-study 1: patients*****with*****clinically significant depressive symptoms (baseline PHQ-9 ≥ 5)**			
Process of care			
Key outcome - components of initial depression care (CIDC): antidepressant prescription and/or mental health referral among participants with baseline PHQ-9 ≥ 10*	X		PQ, PCPQ, MRR
Others			
Antidepressant prescription and/or mental health referral among all sub-study participants*	X		
Follow-up with PCP at an appropriate interval†	X		
Inquiry regarding self-harm/suicidal thoughts	X		
Patient function			
PHQ-8^‡^ score	X	X	PQ
SF-12 Mental Component Summary score		X	
SF-12 Physical Component Summary score		X	
Patient engagement in depression care			
Readiness			PQ
To discuss depression (in general) with PCP	X		
To discuss depression treatment with PCP	X		
Self-efficacy			
For recognizing depression	X	X	
For discussing depression with PCP	X	X	
Provider-patient interaction			PQ, PCPQ, MRR
Discussion of depression	X		
Patient request for depression treatment	X		
Patient perceived depression stigma	X	X	PQ

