**Sub-study 2: patients*****without*****clinically significant depressive symptoms (baseline PHQ-9 < 5)**			
Process of care			
Antidepressant prescription (over-treatment)	X		PQ, PCPQ, MRR
Distraction effects			
Index office visit length	X		
Patient request for depression treatment	X		
Physician visit effort	X		
Patient function			
SF-12 Physical Component Summary score (potential toxicity, i.e. reduced function)		X	PQ
Patient perceived depression stigma (potential reduction)	X	X	PQ

* Sub-study 1 primarily powered to examine this outcome; research evidence indicates PHQ-9 scores ≥ 10 are associated with significant life impairment (e.g. reduced functional abilities) and a strong likelihood of clinical depression, while scores of 5–9 are more equivocal in this regard.

^†^ Not an evidence-based element of care, but endorsed in prevailing clinical practice guidelines.

^‡^ Includes all PHQ-9 items except the item concerning self-harm thoughts.

Abbreviations:

*AMEP2*, Activating Messages for Enhancing Primary Care Practice; *MRR*, medical record review; *NA*, not applicable (participants in this sub-study are not followed up); *PCP*, primary care provider; *PCPQ*, PCP questionnaire; *PHQ*, Patient Health Questionnaire; *PQ*, patient questionnaire.

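### The 80% power stated for a 15-point difference in CIDC counts all patients with PHQ-9 ≥ 5, but CIDC is scored only in those with PHQ-9 ≥ 10

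*Protocol article*

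**What the plan says.** Under Power calculations and sample size, the article states: "By setting target sample sizes of 170 subjects per arm, the effectiveness sub-study was designed to provide 80% power to detect between-arm (pairwise) differences" of 15 percentage points in the proportion receiving CIDC, two-sided, alpha 5%. The same 170 per arm is also said to cover 0.3 sd on continuous outcomes.

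The section on Sub-study 1 fixes the size of that sub-study: "This sub-study involves a sample of approximately 500 patients with a Patient Health Questionnaire-9 (PHQ-9) score of ≥ 5". It then codes CIDC "among the subset of participants with a high likelihood of clinically significant depression", meaning a baseline PHQ-9 of 10 or more, and adds that "the study was powered to detect a significant intervention effect on this outcome".

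Table 1 repeats the restriction for the key outcome: "antidepressant prescription and/or mental health referral among participants with baseline PHQ-9 ≥ 10". A separate row, listed among the other outcomes, takes the same prescription/referral event in all sub-study participants. Both rows carry the asterisk whose note reads "Sub-study 1 primarily powered to examine this outcome".

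**The concern.** The power statement and the outcome definition use different denominators. The 170 per arm matches the whole PHQ-9 ≥ 5 sample, yet the outcome it is said to power excludes everyone scoring 5 to 9. The article gives no separate target for PHQ-9 ≥ 10 and shows no inflation of 170 for the restriction.

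CIDC is the only outcome called key. A reader who relies on the power section would believe that a true 15-point effect on it had a four-in-five chance of detection. If about half the sample is outside the analysis, that chance is much lower.

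**Working it through.** **Inputs**
- Target: 170 per arm, 15 points, two-sided 5%, 80% (Power calculations and sample size). 3 × 170 = 510, against approximately 500 with PHQ-9 ≥ 5 (Sub-study 1).
- Accrued PHQ-9 ≥ 10, from Table 2 (rows 10–14 and 15+): IMCP 66 + 39 = 105; PSA 43 + 31 = 74; control 56 + 33 = 89. Total 268; 268/559 = 48%.
- Same share at the planned size (assumption): 510 × 268/559 ÷ 3 = 81.5, about 82 per arm.
- Control CIDC rate: not stated, so varied.

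**Formula** (two proportions, pooled variance under the null, no adjustment)

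Power = Φ[(d − 1.96·s0)/s1], where d = p2 − p1, s0 = √{p̄(1 − p̄)(1/n1 + 1/n2)}, s1 = √{p1(1 − p1)/n1 + p2(1 − p2)/n2}, and p̄ is the pooled proportion.

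**The plan's own figure.** Take 35% v 50% with 170 per arm: s0 = 0.0536, s1 = 0.0530, so (0.15 − 0.1051)/0.0530 = 0.85 and power is 80.2%. Over control rates of about 30–55%, power is 79–82%. The minimum is 79.2%, at 42.5% v 57.5%. The stated 80% reproduces when all 170 per arm are counted.

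**The same contrast in the subset.** Take 35% v 50%, PSA v control (74 v 89): s0 = 0.0776, s1 = 0.0770, so (0.15 − 0.1521)/0.0770 = −0.03 and power is 48.9%.

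Power for a 15-point difference:

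| Control rate* | 170 v 170 | IMCP v control (105 v 89) | PSA v control (74 v 89) | IMCP v PSA (105 v 74) | Planned share (81.5 per arm) |
|---|---|---|---|---|---|
| 10% | 96% | 78% | 72% | 73% | 72% |
| 20% | 88% | 64% | 58% | 59% | 57% |
| 30% | 82% | 57% | 51% | 53% | 51% |
| 42.5% | 79% | 55% | 48% | 51% | 48% |

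*For IMCP v PSA, the rate in the PSA arm.

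At a control rate of 55% the three accrued contrasts give 58%, 50% and 54%. So at the rates that reproduce 80% with 170 per arm (30–55%), subset power is about 48–58%.

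**Difference detectable with 80% power, accrued sizes** (points):

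| Control rate* | IMCP v control | PSA v control | IMCP v PSA |
|---|---|---|---|
| 10% | 15.4 | 16.9 | 16.5 |
| 20% | 18.3 | 20.0 | 19.5 |
| 30% | 19.7 | 21.5 | 20.8 |
| 40% | 20.1 | 21.9 | 21.1 |

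**The case against.** **Unknown control rate.** At a 5% control rate all three contrasts exceed 80% power for 15 points (84–89%), so the claim is not impossible. This stands as a reason not to prescribe one replacement figure. It does not rescue the stated one: at 5%, 170 per arm would give about 99%. If the 80% was instead meant as a worst-case bound over control rates, the like-for-like bound in the subset is about 48–55% (the 42.5% row).

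**Accrued against planned sizes.** The counts 105/74/89 are results of accrual, while the power section states design targets. Screening invited everyone with PHQ-8 ≥ 10, so a higher share may have been expected. This stands in part, and accrued sizes should be labelled as such. But 170 per arm in the subset would need 510 patients with PHQ-9 ≥ 10, which is the entire planned sub-study.

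**The asterisk.** It also marks the all-participant row, and 80% would fit that row. A reader might infer that the calculation was made for that outcome. The article does not say so: the power section names CIDC, and the footnote justifies itself by the meaning of PHQ-9 ≥ 10. Which outcome was intended is for the authors to state.

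**Null results.** A reader might infer that a non-significant CIDC contrast is inconclusive for differences below about 20 points. That confuses the detectable difference with the confidence interval. With both rates at 30%, the 95% half-width 1.96·√{p(1 − p)(1/n1 + 1/n2)} is 14.1 points for 74 v 89 and 12.9 for 105 v 89; at 40% it is 15.1 and 13.8. At 30%, an observed difference of zero would exclude 15 points. The Planned analytic approach already commits to point estimates and 95% intervals.

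**Model.** The planned analysis has physician random effects and stratum terms, which these figures ignore. That is unlikely to close a gap of this size, but the figures should be called unadjusted.

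**Level of detail.** An article may leave much to a fuller plan. Here, though, a stated figure conflicts with a stated definition, so this is not an omission.

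**Conclusion.** The point holds as a mismatch between the population used for power and the population analysed. It is not an arithmetic slip: 80% is right for 170 per arm and wrong for CIDC as defined. Unadjusted power for a 15-point CIDC difference is about 48–58% at control rates that reproduce the stated 80%, and about 48–78% over control rates of 10–42.5%. The upper end needs a control rate near 10%, where 170 per arm would give 96%.

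These figures rest on assumed control rates, on accrued subset sizes (or the same 48% share of 510), and on no allowance for clustering or stratification. The point concerns what the article claims about power. It does not touch the validity of the analysis or the estimates.

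**What to change.** 1. Power calculations and sample size: say that 170 per arm is the PHQ-9 ≥ 5 sample, and that 15 points at 80% power holds only for a prescription/referral outcome analysed in all of those patients.
2. In the same section, for CIDC in PHQ-9 ≥ 10: give the expected subset size and control rate, and restate the difference detectable with 80% power. With the accrued sizes, labelled as accrued and unadjusted, this is about 18–22 points at control rates of 20–40% and about 15–17 points at 10%.
3. Sub-study 1: bring the sentence that the study was powered on this outcome into line with item 2.
4. Table 1: resolve the asterisk, which marks two outcomes with different denominators, by stating which one the calculation was for.
5. Interpret a null CIDC contrast from its 95% confidence interval, as already planned, and not from a power threshold.

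The cost is wording only. No data collection or analysis changes, but the stated power for the key outcome becomes less favourable.

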### Data safety and monitoring plan

Three categories of patient safety concerns apply to this study: 1) heightened anxiety and possible prolonged visit lengths among patients who are led to believe they have depression but do not (false positives): 2) missed diagnoses of depression (false negatives); and 3) appropriate diagnosis and treatment of patients with moderate, moderately severe, and severe depression, including those experiencing suicidal ideation. The study addressed the potential for longer visit length by reminding physicians of the content of the intervention and suggesting supportive language and resources that could be used with patients wanting to discuss their symptoms. No specific provisions were made to deal with missed diagnoses of depression among those with low PHQ-9 scores, as rates of missed depression would be no higher than in usual care. Regarding suicidal ideation among enrolled patients, when patients responded positively to the suicidality question in the PHQ-9, the research assistant: 1) offered the patient three telephone numbers in the respondent’s local calling area; 2) spoke with the patient about notifying the doctor; 3) initiated a confidential letter to the doctor about the patient’s status (hand delivered to the physician before the patient’s scheduled appointment in the clinic); and 4) notified the project manager, who notified the principal investigator about the event within 24 hours. The PI (or, alternatively, the study physician on call) in turn paged the patient’s primary care physician to discuss care of the patient within two working days.

Beyond threats to patient safety, procedures were established regarding the documentation of untoward events, including breaches of confidentiality. Any known breach of confidentiality was to be reported to the principal investigator within 24 hours. The principal investigator was required to notify the appropriate IRB(s) of all untoward events within one week. These events were also meant to be discussed during regular meetings of the data safety and monitoring board.

### Patient accrual and study flow

Altogether, 867 patients were accrued into the study and randomized successfully (Figure 2), 559 with PHQ-9 scores ≥ 5 for Sub-study 1 and 308 with PHQ-9 scores <5 for Sub-study 2 (Table 2). Randomization was generally successful, with modest between-group differences in baseline characteristics (Table 2).

**Figure 2 F2:**
[figure not shown]
CONSORT diagram.

**Table 2 T2:** Characteristics of participating patients

**Characteristic**	**Interactive-multimedia arm (n = 294)**	**PSA arm (n = 286)**	**Attention control arm (n = 287)**	**p-value**^*****^
% female	162 (55.1)	159 (55.6)	165 (57.5)	0.83
Mean age, yrs (SD)	51.5 (12.4)	52.2 (11.4)	51.7 (11.5)	0.82
Race/ethnicity (%)				0.86
Hispanic or Latino	43 (14.6)	40 (14.0)	40 (13.9)	
Black, not Hispanic	61 (20.7)	50 (17.5)	57 (19.9)	
Asian or other	25 (8.5)	32 (11.2)	33 (11.5)	
White	165 (56.1)	164 (57.3)	157 (54.7)	
Income (%)				0.70
Less than $35,000	106 (36.0)	110 (38.5)	101 (35.2)	
$35,000 or more	188 (64.0)	176 (61.5)	186 (64.8)	
% with college or graduate degree	126 (43.3)	123 (43.2)	142 (49.6)	0.20
% living with spouse or partner	162 (55.9)	160 (56.1)	165 (57.7)	0.89
Site of care (%)				0.51
Specialty Practice	119 (40.5)	130 (45.5)	114 (39.7)	
Academic	94 (32.0)	89 (31.1)	105 (36.6)	
HMO	32 (10.9)	30 (10.5)	24 (10.9)	
VA	49 (16.7)	37 (12.9)	44 (15.3)	
PHQ-8 (SD)				
At enrollment	7.9 (5.4)	7.0 (5.1)	7.2 (5.4)	0.11
At index visit	7.9 (5.5)	6.7 (5.3)	7.1 (5.4)	0.05
*Correlation	0.84	0.84	0.86	
PHQ-9 category, N (%)				0.17
<5	90 (30.6)	109 (38.1)	109 (38.0)	
5-9	99 (33.7)	103 (36.0)	89 (31.0)	
10-14	66 (22.4)	43 (15.0)	56 (19.5)	
15+	39 (13.3)	31 (10.8)	33 (11.5)	
SF-12 at enrollment, Mean (SD)				
Mental Health Score (n = 840)	44.8 (11.8)	47.7 (11.6)	46.3 (12.7)	0.02
Physical Health Score (n = 840)	41.4 (13.5)	41.8 (13.7)	41.2 (13.2)	0.86
Somatic Symptom Severity at Index Visit†, Mean (SD)	7.3 (2.0)	7.3 (2.0)	7.4 (1.9)	0.90
Depression Stigma at Index Visit, Mean (SD)	16.5 (4.0)	16.9 (3.8)	16.5 (3.8)	0.42
Self-efficacy for patient-physician interactions (PEPPI) regarding mental health, Mean (SD)	21.9 (5.8)	21.7 (5.6)	21.8 (5.9)	0.86

^*^To obtain p-values, the F-test statistic in a one-way ANOVA was used for comparing means and the chi-square test for association was used for categorical variables.

†Reflects how much patient was bothered in the past month (theoretical range from 4 to 12) by stomach pain; back pain; pain in arms, legs or joints, and headaches.

### Planned analytic approach

For all outcomes except for antidepressant behavior in the non-depressed patients, analyses will be implemented using multiple regression models for clustered data to account for the nesting of patient-level observations within providers and, for longitudinally assessed outcomes, the nesting of repeated measures within patients. Most analyses will take the form of generalized linear mixed models [73], with logistic regression models estimated via generalized estimating equations [74] used as a robust backup in case mixed-model assumptions are violated or computational difficulties (lack of convergence) are encountered.

In generalized linear mixed models, random effects will be specified for the physician (to account for the nesting of patients within physician). For longitudinal outcomes, random effects will also be specified for patient. The key independent variable will be the study group assignment (control vs. PSA vs. IMCP) and additional independent variables will be included to account for the stratified study design. Wald tests, point estimates and 95% Confidence Intervals will be used to assess hypothesized contrasts among the study arms.

Because the incidence of antidepressant behavior in the non-depressed patients is expected to be very low and the primary contrast of interest is for testing the one-sided noninferiority hypothesis that the incidence is not 3.5 percentage points higher in the combined PSA/IMCP groups versus the control, we will use restricted maximum likelihood methods to construct a 2-sided 90% confidence interval for the PSA/IMCP vs. Control risk difference in antidepressant prescribing risk to assess this null hypothesis, as described by Farrington and Manning [72].

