### Sub-study 2: patients *without* clinically significant depressive symptoms

This sub-study involves a sample of approximately 300 patients whose baseline PHQ-9 scores were less than 5. The aims of this sub-study are:

(1) To examine whether the interventions are associated with (a) detrimental *process of care* effects (including unnecessary initial antidepressant prescriptions, physician rating of greater effort during visit, longer visit duration), and/or (b) decrements in patient functioning (specifically, worse physical health at 12 week follow-up). It is hypothesized that the active interventions will not result in detrimental outcomes in those without evidence of significant depression.

(2) To examine whether the interventions may lessen perceived depression stigma among non-depressed persons. It is hypothesized that the active interventions will result in reduced stigma after the index visit among patients without evidence of significant depression.

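### If requests for depression treatment are rare among non-depressed controls, the planned logistic Wald test is uninformative at zero control requests and underpowered at one or two; a score-type or penalised method should be pre-specified

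*Protocol article*

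**What the plan says.** Under Planned analytic approach, the general rule is: "For all outcomes except for antidepressant behavior in the non-depressed patients, analyses will be implemented using multiple regression models for clustered data". Most analyses are to be generalized linear mixed models with a physician random effect, study arm, and further terms for the stratified design, "with logistic regression models estimated via generalized estimating equations [74] used as a robust backup" if assumptions fail or the model does not converge. For inference, "Wald tests, point estimates and 95% Confidence Intervals will be used to assess hypothesized contrasts among the study arms".

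One Sub-study 2 outcome is exempt. The reason begins "Because the incidence of antidepressant behavior in the non-depressed patients is expected to be very low" and goes on to add that the contrast of interest is a one-sided noninferiority test with a 3.5-point margin. For that outcome, "we will use restricted maximum likelihood methods to construct a 2-sided 90% confidence interval for the PSA/IMCP vs. Control risk difference", by the Farrington-Manning method.

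Table 1 lists a second binary hazard for Sub-study 2 under distraction effects: "Patient request for depression treatment". It is outside the exemption, so the general rule applies. The stated hypothesis for the hazards is: "It is hypothesized that the active interventions will not result in detrimental outcomes in those without evidence of significant depression".

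**The concern.** Sub-study 2 exists to find harm in patients with PHQ-9 below 5. The control arm watches a sleep-hygiene video. The PSA, according to Description of interventions, was designed to prompt patients to seek depression care and ask for information or treatment. Few or no requests in the control arm with several in an active arm is a pattern that this sub-study should be able to recognise.

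Logistic Wald inference handles that pattern badly. With no events in one arm the maximum-likelihood log odds ratio is infinite and its model-based standard error grows faster than the estimate, so the test statistic goes to zero. A physician random effect does not restore a finite estimate. The only stated fallback, GEE, is on the same logit scale. A non-significant result produced in this way could be read as support for the hypothesis of no detriment.

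**Working it through.** **Inputs.** Arm sizes come from the PHQ-9 <5 row of Table 2: IMCP 90, PSA 109, control 109 (199 active v 109 control). The request rate is not in the article, so a range is assumed. All calculations are unadjusted and ignore physician clustering.

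**The plan's own figure.** Power calculations and sample size states that "the target enrollment of 102 subjects per arm provides 80% power to reject the noninferiority null hypothesis". This concerns prescribing, but it shows that the score-type method is already in hand. With 204 v 102, a 1% true risk and a 3.5-point margin, the restricted estimates are 0.0389 and 0.0039.
- Null SE = √(0.0389×0.9611/204 + 0.0039×0.9961/102) = 0.0149.
- SE at 1% in both groups = √(0.0099×(1/204 + 1/102)) = 0.0121.
- Power = Φ((0.035 − 1.645×0.0149)/0.0121) = 80.8%. The stated 80% reproduces.

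**Chance of an empty control cell**, (1 − p)^109, and of at most two control requests:

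| Assumed control risk | No requests | Two or fewer |
|---|---|---|
| 0.5% | 58% | 98% |
| 1% | 33% | 90% |
| 2% | 11% | 63% |
| 3% | 3.6% | 36% |
| 5% | 0.4% | 9% |

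**Zero control requests, 8/109 PSA v 0/109.** If iteration stops at a fitted control risk e, then log OR ≈ ln(8/101) − ln(e) and SE ≈ √(1/8 + 1/101 + 1/(109e)). At e = 10⁻⁹, z = 18.2/3029 = 0.006. The fitted model gives Wald p = 0.999. The score test has pooled risk 8/218 = 0.0367 and SE = √(0.0367×0.9633×2/109) = 0.0255, so z = 0.0734/0.0255 = 2.88 and p = 0.004. Fisher gives 0.007. The Farrington-Manning risk difference is 7.3 points (90% CI 4.2 to 12.6). For pooled active arms, 15/199 v 0/109 gives Wald p = 0.999, Fisher 0.0016, and a difference of 7.5 points (5.0 to 11.2).

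**One or two control requests.** For 8/109 v 1/109, log OR = ln(8×108/101) = 2.146 and SE = √(1/8 + 1/101 + 1 + 1/108) = 1.070, so Wald p = 0.045. The score test gives z = 0.0642/0.0270 = 2.38, p = 0.017. For 15/199 v 1/109, Wald p = 0.037 (Fisher 0.013); for 15/199 v 2/109, 0.053 (Fisher 0.038).

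**Power, PSA v control, 109 v 109**, by exact binomial enumeration at two-sided 5%:

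| Control v PSA risk | Wald | Score | Fisher |
|---|---|---|---|
| 0.5% v 8% | 26% | 86% | 75% |
| 1% v 8% | 36% | 75% | 63% |
| 2% v 8% | 37% | 53% | 42% |
| 3% v 10% | 49% | 58% | 47% |
| 5% v 12% | 43% | 48% | 37% |

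The score test's type I error was at most 5.4% in the scenarios checked.

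**GEE at 15/199 v 0/109.** With fitted control risk stopped at 10⁻³, 10⁻⁶ and 10⁻⁹, the model-based z is 1.4, 0.12 and 0.006, while the sandwich z is 15, 40 and 64. Software runs returned undefined robust standard errors or did not converge.

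**The case against.** Several points stand and limit the claim.

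- **Rarity is assumed.** The 1% risk in the power section and the low incidence in the analysis section both concern prescribing. A prescription needs a physician to act; a request needs only the patient to ask. A reader might infer that requests are rare for the same reason, but the article does not say so.
- **The exemption had two reasons.** Prescribing was set apart for its noninferiority contrast as well as its rarity. Requests have no margin, so the plan does not contradict its own rationale.
- **Few is not none.** A reader might infer that the planned test cannot register harm whenever control requests are few. At 8 v 1 it does (p = 0.045). Impossibility holds only at zero, and only for likelihood-based Wald.
- **Direction.** A reader might infer that the failure always favours no distraction. The GEE fallback can err either way, and an infinite odds ratio is visibly a failed fit.
- **Exact tests.** From about a 3% control risk, Fisher is no better than Wald (47% v 49% at 3% v 10%).
- **Strata.** The article does not list the adjustment terms, and a stratum with no events does not by itself make the arm effect infinite.

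It can also be said that sparse-cell contingencies belong in an analysis plan. That does not remove the point: the article states a rule for every outcome but one, names the test and names the fallback. The point concerns what that rule does.

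**Conclusion.** The point holds conditionally. If the control risk of a request is about 2% or less, the stated Wald inference has a material chance of being uninformative (11% at 2%, 33% at 1%, 58% at 0.5%) and loses power when one or two control requests occur. At 1% v 8% it has about half the power of a score test. The named GEE backup is not a usable remedy under separation. At control risks of about 3% to 5% or more the gap to the score test is 9 points or less in the scenarios shown.

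The conclusion rests on the assumed range of rates and on unadjusted calculations without clustering. It concerns one secondary hazard outcome and does not affect the prescribing analysis or Sub-study 1. The change is worth making because it is cheap and the score test had higher power than Wald in every alternative computed.

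**What to change.** In Planned analytic approach, add a sentence for patient requests for depression treatment in the non-depressed: report arm-specific risk differences with score-type (Farrington-Manning or Miettinen-Nurminen) confidence intervals and a score test. If adjustment for the randomisation strata is wanted, use Firth-penalised logistic regression with profile-likelihood intervals instead. Do not make Fisher's exact test the default.

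The cost is one sentence and reuse of a method already planned for prescribing. The small downside is that the risk-difference analysis carries no physician random effect, which should matter little because patients were randomised individually.
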